#### Experimental group

##### Verum acupuncture

Disposable sterile acupuncture needles (0.25 mm × 40 mm; Hwato brand; Suzhou Medical Supplies Factory Co. LTD, Suzhou, China) were used. “Xing-Nao Kai-Qiao” acupuncture is applied to treat MAAS according to TCM theory. The acupoints include bilateral PC6 (Neiguan), GV26 (Shuigou), affected side SP6 (Sanyinjiao), and CV23 (Lianquan), beside CV23 (left Panglianquan and right Panglianquan), and affected side HT1 (Jiquan), affected side LU5 (Chize), and affected side BL40 (Weizhong).

Acupoints PC6 and BL40 are inserted at a depth of 5–10 mm, acupoint CV23 (left Panglianquan and right Panglianquan) is inserted at a depth of 55 mm, acupoint GV26 is inserted at a depth of 5–10 mm, and the others are inserted at a depth of 25–35 mm. The pecking technique is performed on GV26 to achieve an intense 6–9-s stimulation. In the other group, lifting-pushing and spinning-rotating methods were performed to achieve the “De Qi” sensation, such as pain, numbness, heaviness, swelling, etc. Finally, after 30 min of retention, all needles are removed. Participants will receive treatment for 6 consecutive weeks, 5 times a week.

The manipulators are senior professional doctors with profound background knowledge and rich experience accumulated for many years.

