##### Sham-acupoint acupuncture

Sham-acupoint acupuncture mainly consists of some sham acupoints not located on the meridians and have no therapeutic effect on aphasia. According to the WTO international standards of acupoint selection, we select the acupoints to be studied. Also, with the acupoints as a reference, the lateral opening of 1 cun in the horizontal direction selected non-meridian and non-acupoint as a control study. The stimulating amount of acupuncture requires no “De Qi” sensation. The same procedure is used as that for the verum acupuncture group.

All the members who participated in the study will get a series of formal training on the study protocol, treatment methods, and assessment. All acupuncturists and speech therapists will receive training related to the study prior to recruitment, including the location of acupuncture points, depth, direction of stabbing, frequency of lifting and inserting, and speech training techniques.

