## Discussion

Acupuncture has been increasingly used to treat motor aphasia after stroke in the past two decades [24]. A study found that acupuncture combined with language training could improve the early rehabilitation effect of MAAS [25]. Other studies have demonstrated that specific acupoint stimulation activated the language-related areas in the brain of MAAS patients [26–28].

Although acupuncture has therapeutic effects on aphasia after stroke [24], it has not been recommended in the current stroke guidelines because of methodology limitations in relevant studies [29]. The efficacy of acupuncture requires methodologically rigorous, high-quality RCTs to confirm [4, 11, 30].

To distinguish between the acupuncture and placebo effects, we choose needling 1 cun away from the acupoints of the actual acupuncture group as sham acupuncture; these acupoints are not located on the meridians and do not affect aphasia. Due to the physical stimulation of acupuncture and familiarity of Chinese patients with acupuncture, double-blind and non-penetration sham acupuncture could not be performed in this study. Instead, non-acupuncture and non-meridian acupoint shallow acupuncture are used. However, slight physical stimulation will occur in the location of acupoints that will not affect the evaluation of acupuncture efficacy.

The study will adopt WAB as primary outcomes, commonly used to evaluate language function in clinical practice. WAB uses clinical and neurolinguistic principles to assess the severity of the spoken language deficit in aphasia and has high internal consistency, test-retest reliability, and validity [31]. Both CFCP and BDAE can assess the language ability of aphasia patients. BDAE has been demonstrated to have good discriminant validity in different languages and cultural backgrounds [32]. CFCP can better focus on evaluating the changes in daily life communication of aphasia patients and providing language rehabilitation training guidance [33]. Additionally, patients with TCM treatment will evaluate the neurological function, quality of life, and health status using NIHSS, SAQOL-39, SS-QOL, and HSTCM.

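### The depth stated at CV23 and the points beside it exceeds the only needle named by 15 mm, and the sham depth is described in two ways that cannot both hold

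*Protocol article*

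**What the plan says.** **Verum arm.** Under Intervention description {11a}, Verum acupuncture, one needle size is given: "Disposable sterile acupuncture needles (0.25 mm × 40 mm; Hwato brand". No other length appears anywhere in the article. For CV23 and the points beside it, the text reads: "acupoint CV23 (left Panglianquan and right Panglianquan) is inserted at a depth of 55 mm". The remaining depths are smaller: 5–10 mm for PC6, BL40 and GV26, and 25–35 mm for all other points.

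A sentence on De Qi manipulation comes after the pecking technique at GV26 and begins: "In the other group, lifting-pushing and spinning-rotating methods were performed to achieve". Retention is 30 minutes, with 5 sessions a week for 6 weeks.

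**Sham arm.** Explanation for the choice of comparators {6b} and the Sham-acupoint acupuncture section both place the needles 1 cun from the verum points and both exclude De Qi. The latter section then adds: "The same procedure is used as that for the verum acupuncture group". It gives no depth of its own. The Discussion describes the sham differently: "non-acupuncture and non-meridian acupoint shallow acupuncture are used".

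**The concern.** There are two separate contradictions and one wording error.

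First, an operator holding the named needle cannot reach the stated depth at CV23 and the points beside it. Either the needle or the depth has to give way, and the text does not say which. This is a matter of treatment fidelity. It also bears on safety, because the article permits antiplatelet drugs and lists haematoma among the expected reactions.

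Second, the sham is meant to separate the acupuncture effect from the placebo effect, and the hypothesis in Objectives {7} is superiority over that sham. What a positive result means depends on how the arms differ. If the sham is needled to verum depth, the arms differ in location and De Qi. If it is shallow, they also differ in depth. These are different questions, and the article supports both answers.

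Third, the phrase about the other group sits in the verum section but, read literally, points to the control arm.

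**Working it through.** No sample size, power or error rate is involved. The check compares stated depths with the stated needle length, and then compares the sham descriptions with one another.

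**Step 1. Depth against needle length (Verum acupuncture section)**

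| Points | Stated depth | Within 40 mm? |
|---|---|---|
| PC6, BL40 | 5–10 mm | yes |
| GV26 | 5–10 mm | yes |
| The others | 25–35 mm | yes (largest value 35 mm) |
| CV23 (left and right Panglianquan) | 55 mm | no |

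Excess: 55 − 40 = 15 mm. Relative to the needle: 15 / 40 = 37.5%.

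The sentence is also unclear about its scope. The list of acupoints treats CV23 and the two points beside it as separate entries, whereas the depth sentence puts the two points in brackets after CV23. The 55 mm may apply to all three points or only to the bracketed two. The conflict with the needle is the same on either reading.

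The instruction applies to each planned verum session: 5 × 6 = 30 per participant. That counts how often the text would be applied. It does not measure exposure, because the stated depth cannot be reached with the stated needle.

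**Step 2. Sham descriptions side by side**

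| Feature | Comparators {6b} | Sham-acupoint section | Discussion |
|---|---|---|---|
| Site | 1 cun away | 1 cun lateral, off the meridians | 1 cun away, off the meridians |
| De Qi | none | none | not stated |
| Depth | not stated | as verum, if the same-procedure sentence covers depth | shallow, no figure |

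Site and absence of De Qi are consistent, and shallow needling is compatible with no De Qi. The conflict concerns depth. If the same-procedure sentence covers everything except site and De Qi, the sham inherits 5–10 mm, 25–35 mm and 55 mm. Where verum needling is 5–10 mm, calling the sham shallow might still be consistent with that. Where it is 25–35 mm or 55 mm, a sham at the same depth cannot also be shallow in contrast to verum.

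**Step 3. What the contrast becomes**

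- Same depth as verum: location + De Qi.
- Shallow: location + De Qi + depth.

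**Step 4. The other-group sentence.** Read literally, it gives De Qi manipulation to the control arm and leaves verum with no De Qi technique except at GV26. Both sham sections exclude De Qi, so the literal reading contradicts them. Coming directly after the GV26 sentence and before the verum retention time, the phrase most plausibly means the other acupoints.

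**The case against.** The strongest reply has four parts.

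1. **Most of the treatment is specified.** The points, the remaining depths, the GV26 technique, retention, schedule, sham site and absence of De Qi in the sham are all stated. This stands. A reader might infer that treatment and contrast are undefined, and the article does not support that. What is open is depth at CV23 and the points beside it, and depth in the sham arm.

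2. **The same-procedure sentence has a natural reading.** It follows the sham's own rules on site and De Qi, so it should mean that everything else matches. This also stands, and it rules out a sham with the same manipulation as verum. It does not resolve depth, because matching everything else would include depth. A narrower reading, covering only needle, retention and schedule, would remove the conflict with the Discussion, but the text does not state that limit.

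3. **Training and the full documents may settle it.** Acupuncturists are trained on depth before recruitment, and an investigator manual is mentioned. For this reason the article does not show that the three centres delivered different contrasts, although a reader might suspect it. Nor does it support counting all 252 participants as affected by the 55 mm instruction, since that assumes the sham copies verum depth. Leaving out a sham depth in millimetres would be ordinary condensation in an article. Conflicting statements are not.

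4. **It is late to change delivery.** Recruitment was planned to end on 31 December 2020 and the article appeared on 30 June 2022. If those dates were kept, the 6-week treatments were over before publication. This stands and shapes the remedy.

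**Conclusion.** The point holds in limited form. One verum instruction cannot be carried out as written: 55 mm with a 40 mm needle, an excess of 15 mm or 37.5%. Sham depth is stated inconsistently, so the article does not settle whether the contrast is location plus De Qi, or location plus De Qi plus depth. The other-group phrase is a wording error. It is not evidence that De Qi manipulation was planned for the control arm, since both sham sections exclude it.

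The conclusion assumes that the needle named is the one used at all points, because no other is mentioned, and that the figures are printed as the authors intended. The article gives no basis for putting a size on any bias, loss of power or harm, and none is claimed. The matter still needs correcting because it concerns the operative text of the intervention and the meaning of the comparator, and because correction is cheap.

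**What to change.** 1. Reconcile needle length and depth in the Verum acupuncture section, and state whether the depth sentence covers CV23, the two points beside it, or all three.
2. Reconcile the Sham-acupoint acupuncture section, the comparator rationale {6b} and the Discussion on sham depth, and say what the same-procedure sentence covers (needle, depth, manipulation, retention, schedule).
3. Replace the other-group phrase with what is meant.
4. If any treatment is still to be given, issue the corrected text as an amendment with a training note to all acupuncturists. If treatment is complete, publish a correction and document, by centre, the needle, depth and sham technique actually delivered.
5. Word the trial's conclusion for the contrast that was delivered.

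Which needle, depth or technique is right is for the clinical leads and is not proposed here. The cost is a text correction and, if treatment has finished, retrieval of delivery records from three centres. Sample size and analysis are unaffected.

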#### Control group

##### Language training

Some rehabilitation language training is allowed, such as listening comprehension therapy training and reading comprehension therapy training, which are included in the Operational Specifications for Commonly Used Rehabilitation Techniques (2012 edition). The treatment duration is 60 min each at 5 sessions per week for 6 consecutive weeks.

The procedure is performed by exceptional language therapists who have been professionally trained.

##### Sham-acupoint acupuncture

Sham-acupoint acupuncture mainly consists of some sham acupoints not located on the meridians and have no therapeutic effect on aphasia. According to the WTO international standards of acupoint selection, we select the acupoints to be studied. Also, with the acupoints as a reference, the lateral opening of 1 cun in the horizontal direction selected non-meridian and non-acupoint as a control study. The stimulating amount of acupuncture requires no “De Qi” sensation. The same procedure is used as that for the verum acupuncture group.

All the members who participated in the study will get a series of formal training on the study protocol, treatment methods, and assessment. All acupuncturists and speech therapists will receive training related to the study prior to recruitment, including the location of acupuncture points, depth, direction of stabbing, frequency of lifting and inserting, and speech training techniques.

### Criteria for discontinuing or modifying allocated interventions {11b}

Improved health status: exacerbations, complications, abnormal laboratory results, and adverse events of death from all causes during the observation period.

Withdrawal of participant consent: not being able to visit the clinic for continuous treatment due to inconvenient transportation or a lack of escorts.

### Strategies to improve adherence to interventions {11c}

Through scientifically informed consent, active health education, strengthening humanized care, and making long-term follow-up plans, the subject’s compliance will be improved. We created record cards that included the date of treatment, personal information, and the therapist’s signature to document patient compliance. The participants are also subsidized for transportation expenses.

### Relevant concomitant care permitted or prohibited during the trial {11d}

The patients are prohibited from receiving treatments such as tDCS, NIBS, additional SLT, and some alternative therapies during the intervention period.

### Provisions for post-trial care {30}

Adverse reactions associated with needling include subcutaneous bleeding or hematoma and pain around the needling point. The investigator shall conduct a corresponding examination and symptomatic treatment for the expected adverse effects. Researchers shall take necessary treatment measures according to the condition for possible unexpected adverse events until the adverse events disappear. According to the severity of adverse events, we can choose inpatient, outpatient, home visit, telephone, Internet-based, and other treatment modes.

### Outcomes {12}

#### Primary outcomes

The main observation was the difference between the two groups in WAB [17] scale scores and CFCP [18] scale scores after 6 weeks of treatment to assess the patients’ language abilities and functional communication abilities.

#### Secondary outcomes

The secondary outcome measures were WAB scale scores and CFCP scale scores, assessing the difference between the two groups at 6 months after onset time; Boston Diagnostic Aphasia Examination (BDAE) [19] scores for the severity of the language competence status; Stroke and Aphasia Quality of Life Scale-39 (SAQOL-39) [20] and Stroke-Specific Quality of Life Scale (SS-QOL) [21] scores for the quality of living in stroke patients; National Institute of Health Stroke Scale (NIHSS) [22] scores for the neurological deficit; Health Scale of Traditional Chinese Medicine (HSTCM) [23] scores for the health status, assessing the difference between the two groups after 6 weeks of treatment and 6 months after onset time. The study’s adverse events and dropout causes will be recorded in a case report form (CRF).

### Participant timeline {13}

The participant timeline is shown in Fig. 1.

**Fig. 1 Fig1:**
[figure not shown]
Study design and participation flow chart

### Sample size {14}

Based on the previous pilot study, we expected that acupuncture combined with speech rehabilitation would be more effective than placebo combined with speech rehabilitation [6]. We were assuming that the difference in WAB-AQ values after treatment between acupuncture and placebo is 10.9, with a standard deviation of 22.9 in both groups. According to expert clinical observation, it was found that a superiority margin of 3 for comparisons of acupuncture and placebo for the primary outcome. We performed a superiority test to calculate the appropriate trial sample size with 80% power, *β* =0.2, and *α* = 0.05. The results showed that a clinically significant difference could be detected by a sample size of at least 105 in each group, allowing for a predicted 20% dropout rate. We plan to enroll 252 participants in this study.

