## Statistical methods

### Statistical methods for primary and secondary outcomes {20a}

Baseline characteristics of patients were summarized in groups according to the study data. The chi-square test was used to compare categorical variables, and the 2-sample *t*-test or Wilcoxon rank-sum test was used to compare continuous variables. Analysis of variance for repeated measures was applied according to the outcome of the measurement time, or linear mixed models were used to analyze changes in measurements at different time points. Covariates such as age, duration of illness, and severity of aphasia will be included in the statistical model, correcting the effects of possible imbalances. If there is a violation of the distribution assumption, the appropriate transformation will be used.

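### The margin of 3 WAB-AQ points that sets the sample size is not carried into the hypothesis, primary contrast or analysis, so the stated 80% power is not that of the analysis described

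*Protocol article*

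**What the plan says.** **Sample size {14}.** The section assumes that "the difference in WAB-AQ values after treatment between acupuncture and placebo is 10.9", "with a standard deviation of 22.9 in both groups". It adds a "superiority margin of 3 for comparisons of acupuncture and placebo for the primary outcome", which it attributes to expert clinical observation. It then says: "We performed a superiority test to calculate the appropriate trial sample size with 80% power", with alpha 0.05 and no statement of one or two sides. The result is "a sample size of at least 105 in each group, allowing for a predicted 20% dropout rate", followed by "We plan to enroll 252 participants in this study". The section describes what this number can detect as clinically significant.

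**Objectives {7}.** The hypothesis is that verum acupuncture plus language training is superior to sham plus language training. No margin is named.

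**Outcomes {12}.** The primary contrast is the between-group difference in WAB and CFCP scores after 6 weeks. No margin is named.

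**Statistical methods for primary and secondary outcomes {20a}.** The longitudinal analysis is given as: "Analysis of variance for repeated measures was applied according to the outcome of the measurement time, or linear mixed models were used". Age, illness duration and aphasia severity are covariates. It also says: "If there is a violation of the distribution assumption, the appropriate transformation will be used". No null value, alpha or success criterion is stated.

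**Section {20c}.** This adds intention-to-treat and per-protocol analyses and a comparison of the two. It does not mention the margin.

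**The concern.** A superiority margin changes the hypothesis. With a margin of 3 the trial must reject a true difference of 3 or less. Without it, the trial need only reject zero. The two hypotheses need different numbers of patients and support different conclusions.

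Here the sample size follows the first and the rest of the article reads as the second. Two things are at stake. The 80% power describes a test that the article does not set out. And a p-value below 0.05 from the ordinary group comparison could be reported as the clinically significant superiority for which the trial was sized, although the data need not exclude an effect as small as the margin.

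**Working it through.** **Inputs**, all from Sample size {14}: difference 10.9, SD 22.9, margin 3, alpha 0.05 (sidedness not given), power 80%, 105 per group, 20% dropout, total 252. Allocation is 1:1 (Trial design {8}).

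**Step 1: reproduce 105 per group.** The normal formula is n = 2 × [SD × (z_alpha + z_beta) / d]², with d = 10.9 − 3 = 7.9 if the margin is used and d = 10.9 if it is not. The last column uses the noncentral t distribution.

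| Null | Alpha 0.05 | d | n per group, normal | n per group, t |
|---|---|---|---|---|
| difference ≤ 3 | one-sided | 7.9 | 104 | **105** |
| difference ≤ 3 | two-sided | 7.9 | 132 | 133 |
| zero | one-sided | 10.9 | 55 | 56 |
| zero | two-sided | 10.9 | 70 | 71 |

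For the first row: 2 × [22.9 × (1.645 + 0.842) / 7.9]² ≈ 103.9, so 104; the t version gives 105. Only the margin with one-sided 0.05 yields the stated figure.

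**Step 2: evaluable number.** 105 × 1.2 = 126 per group, or 252 in total, so 105 is the number before the dropout allowance. Losing 20% of 126 leaves 100.8, taken as 101 per arm. If 105 were read as already including dropout, 105 × 0.8 = 84 would be evaluable. At 84, none of the four variants gives 80% power (normal approximation: 72% and 61% with the margin, 93% and 87% without, one- and two-sided respectively).

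**Step 3: power at 101 per arm.** SE = 22.9 × √(2/101) = 3.22, unadjusted. The true difference is 10.9 and power is from the noncentral t.

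| Test | One-sided 0.05 | Two-sided 0.05 |
|---|---|---|
| against zero | 96% | 92% |
| against a margin of 3 | 79% | 68% |

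**Step 4: observed difference needed for success.** The critical t values on 200 degrees of freedom are 1.653 (one-sided) and 1.972 (two-sided).

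- Against zero: 1.653 × 3.22 = 5.3, or 1.972 × 3.22 = 6.4.
- To exclude 3: 3 + 5.3 = 8.3, or 3 + 6.4 = 9.4.

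An observed difference from 5.3 up to 8.3 (one-sided), or from 6.4 up to 9.4 (two-sided), would be significant against zero without showing superiority beyond the margin.

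**Step 5: a true difference of exactly 3.** The test against zero would favour acupuncture about 24% of the time (one-sided 0.05) or 15% (two-sided 0.05). A test of the margin would do so 5% or 2.5% of the time.

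**The case against.** A reader might infer that the hypothesis the trial was sized for is never tested. The article does not support that. Section {20a} states no null, so the zero null is inferred from the default use of the named methods. A linear mixed model yields an estimate and confidence limit that can be compared with 3, and a statistical analysis plan that is not shown may do so. This stands. What remains is a mismatch within the article: the margin determines N and is then absent from the hypothesis, the contrast and the analysis.

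Section {20a} also names the t-test and theWilcoxon test, which may look like further primary tests against zero. That sentence directly follows the one on baseline characteristics and may concern baseline comparisons only. Nothing here rests on it.

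The step 5 figures may be read as an inflated type I error. They are errors only if the margin is the hypothesis. Under the plain superiority in Objectives {7}, acupuncture is superior at a true difference of 3, and a test against zero keeps its nominal level. Nor is that test underpowered: its power exceeds the stated 80%. The fault lies in what a positive result may be said to show.

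The thresholds use an unadjusted two-sample SE. The planned model adjusts for covariates and uses repeated measurements, so its SE would differ and probably be smaller. The figures are illustrative.

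Transformation is allowed only if a distributional assumption fails, so it is a conditional risk. It matters here only because 3 points has no direct meaning on a non-linear scale.

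**Conclusion.** The mismatch holds. The 105 per group comes from a null of 3 points or less at an undeclared one-sided alpha of 0.05, and the margin is not carried into Objectives {7}, Outcomes {12} or section {20a}. As described, the analysis by default tests zero, for which the power at 10.9 is about 96% (one-sided) or 92% (two-sided) at 101 per arm, not 80%. A significant result from it would not establish superiority beyond 3 points; in the illustration the gap in observed difference is 5.3 against 8.3, or 6.4 against 9.4.

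This rests on the article's 10.9 and 22.9, 20% loss from 126 per arm, an unadjusted SE, and the usual zero null of the named methods. It does not show that the margin cannot be tested with the planned model, only that the article does not say that it will be.

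**What to change.** Declare in Sample size {14} whether alpha 0.05 is one- or two-sided, then choose one rule before unblinding.

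- **(a) Keep the margin.** In section {20a}, estimate the adjusted week-6 difference in WAB-AQ on its original scale. Claim superiority only if the lower confidence limit at the declared sidedness exceeds 3. State the power as about 79% (one-sided 0.05) or about 68% (two-sided 0.05) at 101 evaluable per arm. Do not use any transformed analysis for the margin decision.
- **(b) Drop the margin.** Delete it from Sample size {14}, state the zero null, and restate the power as about 96% (one-sided) or 92% (two-sided) at 101 evaluable per arm.

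Either way, align Objectives {7} and Outcomes {12} with the choice. The cost is about a paragraph of wording. Option (a) is the stricter success rule. With one-sided 0.05 it is the rule for which the trial was sized; with two-sided 0.05 its power falls well below the stated 80%, and the article should say so. Option (b) gives up the claim of superiority beyond a clinically chosen margin.

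### The 105 per arm fits only an undeclared one-sided 5% test against the margin of 3, and the dropout step leaves about 101 evaluable per arm (about 79% power), not 105

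*Protocol article*

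**What the plan says.** Under Sample size {14}, the protocol article assumes that "the difference in WAB-AQ values after treatment between acupuncture and placebo is 10.9", "with a standard deviation of 22.9 in both groups". It adds a "superiority margin of 3 for comparisons of acupuncture and placebo for the primary outcome", 80% power and an alpha of 0.05, and names the procedure only as a superiority test: "We performed a superiority test to calculate the appropriate trial sample size". The result is a "sample size of at least 105 in each group, allowing for a predicted 20% dropout rate. We plan to enroll 252 participants". Trial design {8} fixes 1:1 allocation, so 252 means 126 per arm.

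No section says whether alpha is one-sided or two-sided. Statistical methods {20a} lists the t-test and rank-sum test for continuous variables and then says: "Analysis of variance for repeated measures was applied according to the outcome of the measurement time, or linear mixed models were used". It does not mention the margin of 3 or a one-sided level.

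**The concern.** Two things in the printed calculation do not fit together.

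- **The test.** An alpha of 0.05 with no qualifier, next to t-tests, repeated-measures ANOVA and mixed models, is usually read as two-sided. A margin of 3 implies a directional test of whether the difference exceeds 3. These readings need different sample sizes and set different bars for success. If the choice stays open, it could be made after the data are seen.
- **The dropout allowance.** The enrolment figure appears to come from adding 20% to 105. That does not compensate for losing 20% of those enrolled.

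At stake is whether the stated 80% power and the implied 105 evaluable per arm describe the trial as planned. A reader who meets a non-significant primary result will judge it against those figures.

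**Working it through.** **Inputs, all from Sample size {14} except allocation:** difference 10.9; margin 3; SD 22.9; power 80%; alpha 0.05; dropout 20%; 105 per group; 252 in total. Allocation is 1:1 (Trial design {8}).

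**Step 1: reproduce 105.** For two means tested against a margin,

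n per arm = 2 x (z_alpha + z_beta)^2 x SD^2 / (difference - margin)^2,

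with difference - margin = 10.9 - 3 = 7.9, 7.9^2 = 62.41, and 2 x 22.9^2 = 1048.82.

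- One-sided 5%, margin 3: (1.645 + 0.842)^2 x 1048.82 / 62.41 = 103.9, so 104; the exact noncentral t gives **105**. This matches the article.
- Two-sided 5%, margin 3: (1.960 + 0.842)^2 x 1048.82 / 62.41 = 131.9, so 132; exact t gives 133. No match.
- No margin (divide by 10.9^2 = 118.81): 55 one-sided or 70 two-sided; exact t gives 56 and 71. No match.

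Only the one-sided 5% test against the margin gives 105.

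**Step 2: reproduce 252.** 105 x 1.2 = 126 per arm, and 126 x 2 = 252 exactly. The inflation used was n x (1 + 0.20).

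**Step 3: apply the stated dropout.** 126 x 0.80 = 100.8, so about 101 evaluable per arm. To keep 105, the inflation must be n / (1 - 0.20): 105 / 0.80 = 131.25, so 132 per arm and 264 in total. The plan enrols 264 - 252 = 12 fewer, and 12/264 = 4.5%.

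**Step 4: power (exact noncentral t).**

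| Evaluable per arm | One-sided 5%, margin 3 | Two-sided 5%, margin 3 | Two-sided 5%, zero difference |
|---|---|---|---|
| 101 (after 20% dropout) | 78.8% | 68.4% | 92.0% |
| 105 | 80.1% | 70.1% | 93.0% |
| 126 (no dropout) | 86.1% | 77.9% | 96.4% |

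**Step 5: what the choice of test changes.** At 101 per arm the standard error of the difference is 22.9 x sqrt(2/101) = 3.22. With 200 degrees of freedom the critical t values are 1.653 (one-sided) and 1.972 (two-sided). In an unadjusted comparison with the assumed SD, the smallest significant observed difference is:

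- one-sided 5%, margin 3: 3 + 1.653 x 3.22 = 8.3 points;
- two-sided 5%, margin 3: 3 + 1.972 x 3.22 = 9.3 points;
- two-sided 5%, zero: 1.972 x 3.22 = 6.3 points.

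An observed difference of 7 points would succeed under the last test and fail under the other two.

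**The case against.** The strongest reply is that the only proven arithmetic error costs little. Under the one test that reproduces 105, power falls from 80% to 78.8%. That stands.

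It can also be said that a margin and a superiority hypothesis (Objectives {7}) already point to a directional test, that the inputs identify it, and that only one word is missing. This largely stands for the sample size section. It does not cover Statistical methods {20a}, which names analyses normally reported two-sided against zero and drops the margin, so the test used for sizing is not visibly the test to be run.

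The planned model adjusts for age, duration of illness and severity of aphasia, which could recover power. The document gives no correlation, so this is an assumption. A covariate-outcome correlation of about sqrt(1 - 101/105) = 0.195 would restore 80% for the one-sided test against the margin. About sqrt(1 - 101/133) = 0.49 would be needed for the two-sided test against it. The first is modest, so the one-point loss may vanish in practice. The printed calculation does not rely on adjustment, however, and remains wrong as written.

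An unseen analysis plan may state the sidedness. Silence on that alone would be no finding. Here the article prints inputs, a result and an enrolment total that do not agree without an unstated qualifier and a correct dropout formula.

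A reader might go further in two ways that the document does not support:

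- **That the trial has only about 68% power.** This needs a two-sided 5% level combined with the margin of 3, a pairing stated nowhere. If the default two-sided reading of {20a} is followed consistently, the null is zero and power is about 92%.
- **That 105 already includes dropout, leaving 105 x 0.8 = 84 evaluable.** The sentence's grammar allows it, but 252 = 105 x 1.2 x 2 shows that 105 is the number before the dropout allowance, and Step 1 reproduces it as the required evaluable number.

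**Conclusion.** The point holds in limited form and should be fixed. The figure of 105 per arm is the evaluable number for a one-sided 5% test against a margin of 3, which the document does not declare and does not carry into its analysis section. The dropout inflation is wrong: 252 enrolled yields about 101 evaluable per arm, and full protection of 105 would have needed 264. Under the test that reproduces 105, the cost is about 1.2 points of power. The trial is not shown to be badly underpowered.

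The larger uncertainty is which hypothesis the primary analysis will test, since the answer moves power at 101 per arm between about 68% and about 92%. These figures rest on the article's difference, SD and 20% dropout, equal arms, and an unadjusted two-group comparison at the end of treatment.

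**What to change.** Keep 252 and change the wording.

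1. In Sample size {14}, state that 105 is the evaluable number per arm for a one-sided 5% test against a margin of 3 with 80% power.
2. Correct the inflation to n/(1 - 0.20), and state that 252 enrolled gives about 101 evaluable per arm and about 79% power for that test.
3. In Statistical methods {20a}, name the same null hypothesis (margin of 3) and the same sidedness for the primary analysis.
4. If a two-sided 5% level is intended, state that together with the null value and report the matching power at 101 per arm: about 68% against the margin of 3, or about 92% against zero.

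The choice should be recorded before unblinding. The cost is a short text amendment and no extra patients. The stated power becomes one point less favourable if the one-sided margin test is confirmed; under the two-sided options it changes as given in item 4.
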